#### Training of study interventionists

The interventionists for the project are advanced doctoral students with experience delivering CBT-based health interventions and/or trauma-focused therapies (depending on the protocols they are trained to conduct). The health behavior interventionists are familiar with the healthy lifestyle intervention literature and develop a thorough understanding of the protocol for PTSD patients by reviewing the manual and meeting with the PI for training. Interventionists are encouraged to meet with the PI throughout intervention delivery to affirm their knowledge and confidence with the protocol and address any questions that might relate to participant-specific presentations.

For interventionists who conduct the standard trauma therapies, the PI reviews evidence-based conceptual and intervention models of trauma-focused treatment for PTSD, including Cognitive Processing Therapy (Resick et al., 2002; Resick and Schnicke, 1992), Prolonged Exposure Therapy (Foa et al., 2007; McLean and Foa, 2024), and as applicable for participants with a presentation consistent with the literature on complex-PTSD, Contextual Trauma Therapy (Gold and Quiñones, 2020). Trauma therapists are encouraged to review treatment-specific readings for the various models of treatment reviewed during training and meet with the PI and project coordinators (designated as lead interventionists) to discuss treatment options for assigned participants. Trauma therapists select treatment approaches based on the clinical presentations of participants and collaboration with participants about the various options for care. Given the literature suggesting increased rates of drop-out in exposure-based treatment, it was imperative that trauma therapists have a strong rationale for this approach, a deep understanding of its implementation, and the ability to educate the participant about the treatment delivery (Imel et al., 2013). Trauma therapists are invited to discuss their approaches to treatment, ask questions about intervention implementation and participant clinical presentations, as well as discuss relevant research on PTSD treatment during monthly research lab meetings, in one-on-one meetings with the PI, and in peer supervision meetings with the research coordinators.

#### Health behavior/lifestyle intervention

The healthy lifestyle intervention is a 12-session program with sequential but overlapping modules for increasing physical activity, enhancing good nutrition, improving sleep, and improving stress management. The sessions are conducted individually and are held weekly for 90 min. Participants have the option of conducting the intervention sessions (health behavior and/or trauma therapy sessions) in-person or virtually via a secure HIPAA-compliant Zoom platform. The length of the program was determined by the need to be long enough to effectively address the 4 modules, while also being relatively brief to minimize burden for participants and enhance likelihood of compliance. For the current project, the decision to utilize 12 sessions was also informed by positive feedback from the participants and interventionists in the pilot study regarding the program length.

The first module includes psychoeducation on physical activity (health benefits of physical activity and the health risks associated with physical inactivity and overweight) in session 1, as well as implementation of an exercise regimen and discussion of some of the inherent challenges. Participants are encouraged to begin a physical activity regimen that is consistent with recommendations for a healthy lifestyle (aerobic exercise at least 20 min 2–3 times per week). However, interventionists instruct participants to work toward exercise goals that can be incorporated into their lifestyles and maintained. In addition, participants walk for 20 min with the interventionist during intervention sessions 2–5. Session 2 includes discussion of healthy food choices, health risks associated with unhealthy foods, appropriate caloric intake for weight loss (as applicable), reading food labels, fat, vitamin, and sugar content, and setting dietary goals. The interventionist also helps participants distinguish diets from lifestyle changes, emphasize self-monitoring of foods, and helps participants build strategies for nutritional self-control. Nutritional recommendations include a balanced diet, enhancing consumption of fruits and vegetables, and reducing sugars, fat/saturated fat, and caloric intake (as appropriate per participant goals). During sessions 3 and 4, the participant and interventionist work together to analyze current nutritional habits and plan a healthier nutritional plan. Session 3 includes discussion of participant efforts to incorporate physical activity and healthy nutrition into their lifestyle, and the potential for social support to be helpful in behavior change. This session also addresses stress and eating. Interventionists closely monitor the stress coping skills of participants and discuss potential distress associated with giving up previously used unhealthy eating approaches to cope (especially in coping with PTSD symptoms). To address potential desire to be overweight for protection against abuse, alternative methods of achieving a sense of safety are discussed. Session 4 focuses on the skills of shopping for healthy food, planning healthy meals, and reducing behavioral cues/triggers for binge eating and unhealthy eating (e.g., storing foods out of sight, strategies for parties, special events and restaurants, managing emotions). Sessions 5 and 6 will include further discussion of progress and challenges with the physical activity and nutrition regimens.

The sleep-focused intervention begins in session 5 and continues into session 8. In the fifth session, an overview of common sleep problems is introduced, and the participant addresses any sleep difficulties they have had. A rationale for the treatment used in our protocol is provided. During sessions 6 through 8, cognitive behavioral strategies for assisting with sleep improvement are incorporated and discussed. In session 6, participants also identify a problematic nightmare (where applicable) and initiate the process of imagery rehearsal therapy by beginning to develop and write a modified version of the dream. In addition to discussion of insomnia treatment strategies in sessions 7 and 8, participants continue to develop their modified dream and rehearse it in session. Participants are also instructed to rehearse the modified dream daily for 5–20 min.

Sessions 9–12 focus on stress management, relapse prevention, and other issues related to termination of the program. During session 9, the interventionist provides an overview of the cognitive-behavioral model of stress and initiates a discussion of various aspects of the model (e.g., negative thoughts, negative emotions and their relationship to behavior). Between sessions 9 and 10, participants are asked to self-monitor negative thoughts to provide a basis for follow-up discussion in session 10, which focuses on common patterns of negative thoughts and associated negative feelings. During session 10, participants are also familiarized with thought logs (Beck, 2021), which use personal situations identified by participants to assist in identifying relationships between negative thoughts, negative feelings, and behavioral outcomes, as well as constructing responses to stressful situations that are more adaptive. Participants are given homework to complete two or more thought logs between sessions 10 and 11, and the results are discussed during session 11. During session 12, discussion of thought logs and stress coping is continued for the first part of the session. The last portion of the final session includes a review of the skills learned, discussion of risks for relapse and skills for relapse prevention, and discussion of any remaining concerns associated with termination of the intervention program.

### Adherence and strategies for retention

Participants randomized to the experimental (health behavior intervention) arm of the proposed project have the potential to be helped by the program in terms of their physical and mental health. It is expected that the health behavior program and the opportunity to receive free trauma therapy on a time-limited basis are elements that enhance retention (in addition to the gift card incentives). However, given that the study's objective is to determine the effectiveness of the experimental intervention, it is not possible to estimate the extent to which direct benefits will occur. At each assessment session, participants also receive educational materials about their cardiovascular risk assessment results (e.g., # of risk factors, lipid profile, blood pressure).

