## Methods

### Participants

We plan to randomize a total of 212 participants, ages 18 and over, to the two study conditions. Anticipated demographics of the overall sample, based on current data from proposed recruitment sites and prior studies recruiting from the PTSD population, are ages 37 ± 10 (mean ± SD), approximately 72% female, avg. of 12th grade education ± 3 years, and race/ethnicity composed of 64% Caucasian, 21% Hispanic-White, 10% African-American, 3% Caribbean Black, and 2% Hispanic-Non-White. Adults ages 18 and older are recruited from the community, local clinics, and via online advertisements. Criteria for inclusion are: PTSD or subthreshold PTSD [evidenced by ≥ 4 PTSD symptoms (including ≥ 1 re-experiencing symptom) endorsed as 2 or higher (moderately bothersome) on the Posttraumatic Stress Checklist (PCL-5)], the presence of at least one health risk (low physical activity, nutrition does not meet standard recommendations, overweight, sleep disruption), and ability to exercise at a moderate level. Concurrent trauma-focused psychotherapy is required through the 12-week intervention phase of the project and is provided by the project if the participant is not already receiving trauma-focused therapy in the community. On an ongoing basis, the project coordinator verifies the therapy and frequency. Although chronic illnesses are not exclusionary, medications for controlling lipids or blood pressure (e.g., beta blockers, diuretics, ACE inhibitors, statins, PCSK9 inhibitors) are exclusionary, as they would impact the lipid and blood pressure outcomes. Participants may be considered if they are able to consult with their medical provider about temporarily discontinuing these medications long enough for the medication to not be active in the system. Comorbid psychiatric conditions (e.g., depression, personality disorders, substance use disorders) are not exclusionary, as this would result in an unnaturally narrow selection of participants with PTSD. Consistent with standards for intervention studies in PTSD (Mulick and Naugle, 2010; Resick et al., 2002, 2015), those on psychopharmacological medications will be included if the regimen has been maintained as stable for ≥2 months prior to enrollment. This study is approved by the appropriate University Institutional Review Board (IRB). Written informed consent is obtained from all participants at the time of the first outcome assessment (baseline) by the laboratory research assistant(s). As with any human research, a participant may discontinue either intervention condition or any other aspect of the longitudinal study at any time, regardless of the reason.

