
### Study design

This intervention study examines the effects of a 12-session healthy lifestyle behavior program (focused on physical activity, nutrition, sleep, and stress management) administered in an individual format as an adjunct to usual care psychotherapy (one healthy lifestyle session per week), compared with a usual care psychotherapy-only control condition. The control group will only attend the outcome assessments and usual care psychotherapy sessions. Therefore, the design relies on a between-groups comparison of the two conditions. Referrals for continued care/therapy beyond the study intervention phase are provided by the study team, and participants assigned to the control group are eligible to complete the health intervention after the conclusion of their participation in the control arm.

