#### Summary

Completing 162 protocols (81 per condition) with minimum power of 80% and alpha level of 0.05 will permit detection of a moderate effect of 0.47 or greater (Cohen, 1988). Therefore, this sample size would permit detection of the smallest effect estimated above for lipids (*d* = 0.50) and will be conservative for the projected large effects for some of the estimates above. Participants in the health behavior intervention condition (experimental group) are considered treatment completers if ≥75% of sessions are attended.

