#### Data analysis plan

Preliminary analyses will be conducted to examine distributions, detect outliers, and compare the study groups on demographic variables, comorbid psychopathology, type of trauma therapy received, smoking, and alcohol use. Based on the randomization, no differences for demographic (e.g., age, gender) or other baseline comparison variables are expected. In addition, gender is not predicted to interact with the main study effect (condition). If there are group differences in any of the baseline comparison/control variables, the respective variable(s) will be treated as a control in the analyses.

A between-groups approach is used, with study condition as the independent variable (IV) and changes in the outcomes as the dependent variable(s) (DVs). The outcomes will be analyzed using linear mixed-effects regression. This approach is recommended for between-group longitudinal trials with follow-up time points to model changes over time, to incorporate all available data at each time point, and to account for non-independence of observations inherent in repeated-measures data (Verbeke and Molenberghs, 2000). A piecewise model will be specified to model change during distinct time periods of the trial (Raudenbush and Bryk, 2002). Separate slopes will be provided for the pre- to post-treatment phase, and each follow-up point (pre- to 6-month follow-up, and pre- to 12-month follow-up). Multivariate analyses will be used for each hypothesis to control for type 1 error by testing the DVs together. Significant multivariate effects will be followed with univariate tests.

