Overall, the present project will provide essential data to evaluate whether a health behavior program can produce consistent improvements in stress that exceed standard care for adults with PTSD. There are several methodological strengths that permit a thorough evaluation of changes in health risks over time. Including a 9-month longitudinal follow-up period permits better detection of longer-term changes in stress and other health-related outcomes. The use of objective sleep and physical activity monitoring using the ActiGraph technology provides a stronger basis for evaluating the changes in these parameters than self-report alone for the present study (Eid et al., 2021).

In conclusion, the present study entails an extensive evaluation of cardiovascular health risks in adults with PTSD. It provides a valuable assessment of the effects of a health behavior intervention designed specifically for this population. The study results will inform multidisciplinary and/or multicomponent intervention that may have a significant impact on quality of life for patients with PTSD.

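### New project-provided therapy and ongoing community therapy are pooled, and adjusting only when the arms differ leaves any difference between them in the residual; the 6- and 12-month contrasts need wording to match

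*Protocol article*

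**What the plan says.** The Participants section of the protocol article requires trauma-focused psychotherapy through the 12-week intervention phase. It adds that this therapy "is provided by the project if the participant is not already receiving trauma-focused therapy in the community". The section on adherence and retention counts "the opportunity to receive free trauma therapy on a time-limited basis" among the things expected to keep people in the study. For the period after the phase, Study design states: "Referrals for continued care/therapy beyond the study intervention phase are provided by the study team". No section requires or supplies trauma therapy during follow-up.

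Under Recruitment and enrollment, allocation is by coin flip after the first phone contact. No stratification is described, and neither participants nor investigators are blinded.

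The Data analysis plan takes condition as the independent variable and change in the outcomes as the dependent variable. On timing it says: "Separate slopes will be provided for the pre- to post-treatment phase, and each follow-up point", meaning baseline to 3, 6 and 12 months. The arms are first compared on a list of variables that includes the type of trauma therapy received, and a variable enters the model only if the arms differ on it. Neither therapy source nor new versus ongoing status is named.

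**The concern.** The background treatment shared by the two arms consists of two regimens: a course that begins at entry and a course already under way. Because the dependent variable is change from baseline, someone who has just started trauma therapy may change more by month 3 than someone continuing. This is most plausible for PTSD symptoms, depression, stress and sleep. A prognostic factor that happens to be balanced between the arms still adds residual variance, and a rule that adjusts only after finding a difference never removes it.

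The one therapy variable that is listed does not fill the gap. Type is naturally read as modality. For project therapy, the section on training of interventionists has the therapist choose the approach with the participant. That choice follows entry in an unblinded trial, so type is a poorer covariate than a status that can be fixed before allocation.

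There is also a question of meaning. The Introduction hypothesises benefit over and above standard trauma therapy. After week 12 the therapy background is a mix of ended, referred and continuing care, so the later contrasts answer a somewhat different question from the 3-month one.

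**Working it through.** **The plan's own figure.** The Summary of the power section gives 81 completers per arm, "minimum power of 80% and alpha level of 0.05", and says this "will permit detection of a moderate effect of 0.47 or greater". Sidedness is not stated; two-sided is assumed, with a two-group comparison of means at one time point and total SD of change 1.

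- Power = Φ(d / (SD × √(2/81)) − 1.96). With √(2/81) = 0.1571, d = 0.47 and SD = 1, this is Φ(2.991 − 1.96) = Φ(1.031) = 84.9%. The t-test gives 84.5%.
- The effect detectable with 80% power is (1.960 + 0.842) × 0.1571 = 0.440 (t-test 0.443).
- For d = 0.47 at 80% power, 72-73 per arm would do. The stated figure is therefore conservative, and true as worded.

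**Variance left in the residual.** Two inputs are not in the documents and are assumed:

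- p = share of participants starting project therapy;
- D = difference in mean change between the two therapy groups, in within-group SDs.

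Then R² = p(1−p)D² / (1 + p(1−p)D²), and the adjusted SD is √(1−R²). For p = 0.5 and D = 0.5: 0.25 × 0.25 = 0.0625; R² = 0.0625/1.0625 = 5.9%; adjusted SD = 0.970; power = Φ(2.991/0.970 − 1.96) = 86.9%.

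| p | D | R² | Adjusted SD | Power at d = 0.47 | Detectable effect at 80% |
|---|---|---|---|---|---|
| any | 0 | 0% | 1.000 | 84.9% | 0.440 |
| 0.2 | 0.2 | 0.6% | 0.997 | 85.1% | 0.439 |
| 0.5 | 0.5 | 5.9% | 0.970 | 86.9% | 0.427 |
| 0.5 | 0.8 | 13.8% | 0.928 | 89.6% | 0.409 |
| 0.5 | 1.0 | 20.0% | 0.894 | 91.7% | 0.394 |

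As a sample-size equivalent, adjustment is worth a fraction p(1−p)D² more participants: 0.6% in the second row, 6.25% in the mid case, 25% in the last row.

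**Chance imbalance.** The standard error of the difference between arms in the share of new starters is √(2p(1−p)/81). This is 0.079 at p = 0.5 and 0.063 at p = 0.2 or 0.8, with 95% limits of 15 and 12 percentage points. At D = 0.5 such an imbalance moves a single trial's estimate by 0.154 × 0.5 = 0.077 or 0.123 × 0.5 = 0.062 SD. This is another view of the same omitted covariate. It is random error that the unadjusted standard error already covers, and must not be added to the loss above.

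**Effects by therapy source.** With p = 0.3, 0.3 × 81 ≈ 24 completers per arm are new starters. The effect detectable in that subgroup with 80% power is 2.802 × √(2/24) ≈ 0.8 SD.

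**The case against.** The strongest reply is that nothing here is invalid. Both arms have the same therapy rule and are randomized, so source is balanced in expectation and every contrast is unbiased for adding the program to this background. Power at d = 0.47 exceeds the stated 80% without any adjustment. Both inputs are assumed. The article also gives reason to expect little difference for some outcomes: its Introduction cites Veterans whose PTSD symptoms improved without significant improvement in CVD risks, and says that PTSD therapies have not typically addressed sleep directly. Source is an imperfect proxy too, since no minimum time in community therapy is set and a community patient may have only just started. Finally, further covariates can be left to the full protocol or analysis plan.

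Most of this stands, and it limits the point to precision and wording. It does not remove the point, because the article fixes a covariate rule that cannot recover precision from a balanced factor. The proxy problem is met by recording new versus ongoing status as well as source.

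A reader might infer more in three ways, none supported:

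- **That the later contrasts are biased.** They are not, for the reason given.
- **That project-therapy participants lose their therapy at week 12.** The text says time-limited, gives no end date and provides referrals. Community patients may also stop.
- **That the Discussion claims superiority to standard care at 9 months of follow-up.** It says the data will evaluate whether the program "can produce consistent improvements in stress that exceed standard care for adults with PTSD". The sentence on the 9-month follow-up is separate and speaks only of detecting longer-term change.

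**Conclusion.** The point holds as one of precision and interpretation. New and ongoing therapy are pooled, and the stated adjustment rule leaves any difference in change between them in the residual. The loss is roughly 1-20% of variance for assumed shares of 0.2-0.8 and differences of 0.2-1.0 SD. The upper end needs an even split and a full-SD difference together. The mid case is about 6% of variance, or 2 power points at d = 0.47, and the loss is nil if the groups change alike. It is most likely to matter for stress, sleep and psychological outcomes, and may be near zero for vascular measures, lipids and blood pressure.

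At 6 and 12 months the contrast is a valid estimate of adding the program to a 12-week therapy period followed by whatever care occurs. The article does not present it as a test on top of continuing therapy, and the reports should not either.

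**What to change.** - **Phone screen (Recruitment and enrollment):** record therapy source (project-provided or community) and new versus ongoing status before the coin flip. Allocation precedes the baseline visit and is unblinded, so a status first recorded at that visit would not be a secure baseline covariate.
- **Data analysis plan:** enter this variable and its interaction with time as prespecified fixed terms, whether or not the arms differ, at least for the stress, sleep and psychological outcomes.
- **6- and 12-month visits:** ask about current trauma therapy, alongside the existing medication-change question. Report it by arm as description only; it arises after allocation and should not be a covariate. The coordinator's ongoing verification may supply this if it continues past week 12, which the article does not say.
- **Conclusions:** describe the follow-up contrasts as the effect of adding the program to a 12-week therapy period followed by whatever care occurs.
- **Effects by source:** if reported, specify a source-by-condition-by-time term and label the results exploratory, given the imprecision shown above.

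The cost is a short screening item, one added question at two existing visits, a few model degrees of freedom and a narrower follow-up claim.
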